## Methods/Design

### Design of the study

The study is a cluster randomized intervention trial with an institution as the unit of randomization. A random sample of 12 (residential) care homes accommodating a total of 120-180 somatic as well as psycho-geriatric residents in The Netherlands as well as in Flanders (Belgium) are randomly allocated to an intervention or control group. Representative samples of 30 residents in each of the 24 (residential) care homes are monitored during a 6-months period. Research data are gathered at baseline and at 6 months after the start of the study. The study is supervised and monitored by 2 investigators, the first and second author of this article. In each institution, an institution study supervisor, appointed by the managing director, is responsible for executing all study activities. The intervention consists of supervised implementation of the guideline "*Oral health care (residential) care homes for elderly people*" and a daily oral health care protocol. This protocol is derived from the guideline and formulated by the authors. Primary outcome variable is the oral hygiene level of the participating residents. To determine the stimulating or inhibiting factors of the implementation project and the nurses' and nurse aides' compliance and perceived barriers, a process evaluation is carried out [49]. The study is conducted according to the principles of the Declaration of Helsinki (version 17c, 2004) and in accordance with the Medical Research Involving Human Subjects Act (WMO). The study protocol is approved by the Ethics Committees of the Ghent University, Belgium (OG017 - approval 2008/440) and the Radboud University Nijmegen, The Netherlands (NL24666.091.08 approval 2008/273).

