### Participants and setting

In each country, a sample of (residential) care homes for elderly people is obtained using stratified (geographical distribution) cluster sampling with replacement. A (residential) care home is considered eligible for inclusion unless any of the following exclusion criteria are applicable:

• The management of the institution does not agree with the random allocation to the intervention or control group;

• The institution has mainly wards accommodating less than 20 residents;

• The institution has only somatic or psycho-geriatric wards;

• An oral health care guideline or protocol has already been introduced and implemented;

• Nurses and nurse aides have received special training on oral health care during the last 24 months;

• More than 5 other major care innovation projects have been implemented during the last 24 months.

Once the managing director of an institution agrees to participate by written informed consent, the institution is randomly allocated to either the intervention group or the control group of the country. Based on the power calculation (see following indentation) a representative cohort of 30 residents of the institution needs to be included.

Crucial factors for calculating the sample size (n) are the presumed distribution of the outcome measure (oral hygiene level) in the population of residents (*σ*), the presumed effect of the intervention (*μ*^1 ^- *μ*^2^), the power required (1-*β*), the a priori determined level of significance (*α*), and the value of the intraclass correlation (design effect). An a priori power of 80% and a level of significance of 0.05 are predetermined. The design effect (Deff) represents the ratio of the number of residents required using cluster randomization to the number of residents required using individual randomization.

The primary formula for calculating the sample size is: .

Deff = 1 + [(m - 1) *ρ*]; m = the number of residents in each institution, *ρ *= the intraclass correlation coefficient.

The adjusted sample size (n^adj^) equals: n × Deff. The number of residents in each institution (m) = n^adj ^: k; k = the number of institutions in the sample.

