Based on previous studies, an intraclass correlation coefficient of 0.95 and a standard deviation (sd) for dental plaque and denture plaque of 0.75 and 0.88 respectively is used. A 25% improvement of oral hygiene level is the presumed effect of the intervention. With regard to the design effect and drop-outs, loss to follow up, and uncertainty in power calculation, a sample size of 360 residents and 12 clusters per country seems an achievable number for the 6-months period. This means 30 residents per (residential) care home.

To participate in the study, a resident should:

• Supply a written informed consent, undersigned by himself or his legal representative

• Have teeth and/or partial or complete dentures

• Have the cognitive and physical condition required for undergoing an oral examination

• Be residing in the institution during the entire 6-months period presumably.

Residents are excluded when in day-care, in short-term residency, in coma, in palliative care or terminally ill, using a denture adhesive, expressing verbal or physical resistiveness before or during an oral examination.

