### Intervention

The intervention consists of supervised implementation of the guideline "*Oral health care in (residential) care homes for elderly people*" and the daily oral health care protocol derived from the guideline. In each institution of the intervention group, every ward head appoints a nurse who will act as ward oral health care organizer (WOO). The managing director, physician(s), ward heads, WOO's, nurses, nurse aides, and a sample of 30 residents are involved in the study. The implementation of the guideline is supervised by a dental hygienist and includes:

• A 1.5-hour informative oral presentation on the guideline, the daily oral health care protocol, and the supervised implementation project before the start of the study, introduced by the dental hygienist and one of the investigators and addressing the managing director, the institution study supervisor, the ward heads, and the WOO's. Important objective of the informative oral presentation is to lay a strong institutional foundation of the implementation project and the study.

• A 2-hour lecture and in total 3 hours of practical education for the WOO's. The education, presented by the dental hygienist, regards the theoretical and practical essentials of the guideline. The WOO's are practically educated in skills facilitating them to practically educate and encourage the nurses and nurse aides of theirs wards.

• A 1.5-hour theoretical and executive education session at each ward, presented by the WOO, for all ward nurses and nurse aides. This education session is scheduled after the baseline data collection. A summary of the guideline is presented and all executive actions, such as tooth brushing, are taught and demonstrated with ward residents on site. As from the education session, the WOO will encourage and assist the nurses and nurse aides regularly in the daily delivery of oral health care.

• Providing oral health care materials and products for each resident by the dental hygienist.

• Monitoring visits of the dental hygienist and an investigator every 6 weeks, meeting the institution study supervisor and WOO's for listing and resolving implementation and study problems.

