### Data collection

Research data are gathered in the institutions of the intervention and the control group. At baseline, a questionnaire on the resident capacity of the institution, the mean length of stay of the entire group of residents, mean age of the entire group of residents, and the presence of oral health care providers is completed by the managing director of each institution. At baseline and at 6 months, an oral examination of the random sample of 30 residents is carried out by a team of trained external examiners (dentists, master dental students, and master dental hygiene students). They will carry out the data collection after exercising and calibrating the examination criteria and after determining their intra- and inter-examiners' reliability in a pilot study. The examiners do not know whether an institution is allocated to the intervention or the control group. At baseline, a questionnaire on personal and medical details of every resident of the random sample is completed. Furthermore, at baseline and at 6 months a questionnaire addressing the nurses and nurse aides is completed. Finally, at the end of the study, a process evaluation is conducted in the institutions of the intervention group to acquire insight in the stimulating and inhibiting factors of the implementation process. Figure 1 presents a flowchart of the study protocol and Table 1 presents an overview of the data collection.

**Table 1 T1:** Overview of data collection

Data	Collection time	Purpose
**Institution questionnaire ** resident capacity mean length of stay of residents mean age of residents presence of oral health care providers	baseline baseline baseline baseline	comparison institutions comparison institutions comparison institutions comparison institutions

**Nurses and nurse aides questionnaire** gender age years of experience oral health knowledge attitude to personal oral health care	baseline/6 months baseline/6 months baseline/6 months baseline/6 months baseline/6 months	comparison nurses and nurse aides comparison nurses and nurse aides comparison nurses and nurse aides intervention effect intervention effect

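### Homes appear to be allocated, and intervention-home staff briefed, before residents are consented and screened, and nothing keeps the arm from those involved

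*Protocol article*

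**What the plan says.** - **Allocation.** Under Participants and setting: "Once the managing director of an institution agrees to participate by written informed consent, the institution is randomly allocated" to one of the two groups of its country. No resident-level step is named before this.
- **Residents.** The next sentence says that "a representative cohort of 30 residents of the institution needs to be included". The eligibility list that follows requires each resident to "Supply a written informed consent, undersigned by himself or his legal representative". It excludes, among others, residents "expressing verbal or physical resistiveness before or during an oral examination".
- **Who runs the study in a home.** Design of the study: a study supervisor, appointed by the managing director, "is responsible for executing all study activities".
- **Intervention timing.** Under Intervention, the first component is a 1.5-hour presentation covering the guideline, the daily care protocol and "the supervised implementation project before the start of the study". It is given to the director, the study supervisor, the ward heads and the WOOs. The WOOs' own training (a 2-hour lecture and 3 hours of practice) and the supply of care materials carry no date. For the ward session for nurses and aides: "This education session is scheduled after the baseline data collection".
- **Safeguards.** Data collection: "an oral examination of the random sample of 30 residents is carried out by a team of trained external examiners", and these examiners are unaware of each home's allocation.

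**The concern.** Randomising homes balances the homes. It does not balance the residents who enter if they are consented and screened after the arm is known. Consent by a resident or a legal representative, fitness for examination, expected length of residence and resistiveness all leave room for persuasion or judgement. If staff in one arm approach these steps differently, the residents compared at 6 months differ for reasons other than the intervention. An examiner who does not know the arm will measure that difference faithfully.

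The second issue is whether baseline is wholly pre-intervention. One component is placed before the start of the study, and WOO training could fall on either side of baseline. Nurses' knowledge and attitude are outcomes under research question 2 and are measured at baseline and 6 months. A baseline that already contains some intervention effect would shrink a change-from-baseline contrast.

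**Working it through.** The point concerns the order of events. The plan has no figure to reproduce, so the sections are set side by side.

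| Step | Timing in the article | Section |
|---|---|---|
| Director consents | First | Participants and setting |
| Home allocated | Triggered by that consent | Participants and setting |
| Presentation to director, supervisor, ward heads, WOOs | Before the study starts | Intervention |
| WOO training | Not dated | Intervention |
| Supply of care materials | Not dated | Intervention |
| Resident sampling, consent, exclusions | Not dated; described after allocation | Participants and setting |
| Baseline examination and questionnaires | Baseline | Data collection |
| Ward session; WOO support of daily care begins | After baseline | Intervention |
| Second examination and staff questionnaire | 6 months | Data collection |

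**Step 1, resident entry.** Allocation is fixed to an event before any resident step is mentioned. No section places resident consent before allocation, or withholds the arm from those who handle it. The person in charge of study activities in an intervention home is among those briefed on the project.

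**Step 2, what the safeguards cover.** The random draw governs who is selected. It does not govern who then consents or is excluded. Examiner blinding governs measurement. The Discussion raises selection bias for clusters and loss of homes, but not resident selection after allocation.

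**Step 3, the resistiveness exclusion.** The Background links repeated resistiveness to inadequate daily oral care, so this criterion is related to the outcome. It stands in the eligibility list, which points to entry. Its wording does not say which of the two examinations it refers to.

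**Step 4, baseline.** Staff who give daily care are first taught after baseline, and WOO encouragement starts from that session. No documented route therefore leads to a change in residents' plaque before baseline. For knowledge and attitude there is a possible route: WOOs are nurses, and they attend the presentation and may be trained before the baseline questionnaire. Whether they complete that questionnaire is not stated.

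**Step 5, can the size be fixed?** For illustration only, suppose a fraction f of residents with the worst prospects is left out in one arm, and the selecting trait has correlation r with plaque within homes:

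shift = r × SD × √(1 − ICC) × φ(z₁₋f)/(1 − f)

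The SDs (0.75 dental, 0.88 denture) and the ICC of 0.95 are from Participants and setting. The values f = 0.1 to 0.3, r = 0.3 to 0.5 and an alternative ICC of 0.05 are assumptions. The last factor is 0.1755/0.9 = 0.195 at f = 0.1 and 0.348/0.7 = 0.497 at f = 0.3.

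- ICC 0.05, √0.95 = 0.975. Dental: 0.3 × 0.75 × 0.975 × 0.195 = 0.04, up to 0.5 × 0.75 × 0.975 × 0.497 = 0.18. Denture: 0.05 to 0.21.
- ICC 0.95, √0.05 = 0.224. Dental: 0.3 × 0.75 × 0.224 × 0.195 = 0.01, up to 0.5 × 0.75 × 0.224 × 0.497 = 0.04. Denture: 0.01 to 0.05.

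The answer runs from negligible to appreciable, depending on inputs that the article does not give. The presumed 25% improvement has no stated reference mean, so the shift cannot be expressed as a share of the target either.

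**The case against.** The strongest reply has four parts.

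- **The sequence for residents is inferred.** The sentence after allocation concerns sample size and bears no date, and a condensed article may leave recruitment logistics to the full protocol. This stands as a limit on how firmly the point can be put. It does not remove the point, because the article does state the trigger for allocation and the early briefing.
- **The 30 are a random sample, examined by blinded outsiders.** This stands. It removes free choice of residents by staff, if carried out as written, and leaves consent, refusal and exclusion as the open route. The article nowhere says that staff choose whom to approach. Covariates from the resident questionnaire will also be in the analysis, but they adjust only for what was measured.
- **The baseline of the primary outcome is protected.** A reader might infer that early intervention contaminates baseline plaque. The documents do not support that, since teaching of care staff and WOO support both follow baseline. The supply of materials is undated, but nothing places it earlier.
- **Resistiveness is an entry criterion.** A reader might infer that residents who resist at 6 months are removed from the trial. The criterion sits with day-care, coma and palliative care among conditions for entry, and no text orders later removal. What remains is wording that needs one clarifying sentence.

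**Conclusion.** The point holds in a limited form. Taken in the order in which the article describes it, the plan leaves a route to differential consent, refusal and exclusion of residents by people who know the arm. The random sample and blinded examination narrow that route without closing it. This rests on two readings: that resident consent follows allocation, as the order of the text suggests, and that home staff take part in it, as the study supervisor's remit suggests.

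For baseline, the supported statement is that it may not be fully pre-intervention. This applies chiefly to staff knowledge and attitude, and only if WOOs complete that questionnaire. Any such effect would pull a change contrast toward no difference and would leave a comparison of 6-month levels untouched.

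Neither the size nor the direction of a selection bias can be fixed from the documents. The illustrative range of 0.01 to 0.21 plaque points rests on assumed selection and correlation, and it moves several-fold with the ICC. It should not be read as an estimate. A reader might also infer uneven arms from homes being allocated as they consent. The article does not say that allocation is unrestricted, and arm balance is a separate question.

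This is an inexpensive improvement to the order of steps. It does not show that the comparison is invalid.

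**What to change.** 1. In each home, draw the random sample, obtain resident consent, apply the exclusions, and complete the baseline examination and staff questionnaire before the arm is disclosed. Alternatively, have residents recruited by someone unaware of the arm.
2. Hold the presentation and the WOO training after baseline, and date the supply of materials relative to baseline.
3. State that the resistiveness exclusion applies at baseline eligibility only. A resident who cannot be examined at 6 months stays in the assigned arm with a missing value.
4. Report refusals and exclusions by arm, and name resident-level selection beside cluster-level selection in the Discussion.

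These are steps already planned, put in a protected order. Disclosure can be made home by home, so no home need wait for all 12 in its country. The cost is a short delay before the intervention starts in each home, and some extra record-keeping on residents who are drawn but not enrolled.

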### Aim and objectives

The overall aim of the study is to compare a supervised versus a non-supervised implementation of the guideline "*Oral health care in (residential) care homes for elderly people"*. The aim can be rendered into 5 research questions:

1. Is there any statistically significant difference between oral hygiene levels of elderly residents in (residential) care homes with supervised implementation of the guideline when compared to those in (residential) care homes without supervised implementation of the guideline?

2. Is there at care home level any statistically significant difference between attitude and knowledge level of nurses and nurse aides of (residential) care homes with supervised implementation of the guideline when compared to those in (residential) care homes without supervised implementation of the guideline?

3. Is there any statistically significant difference in impact on the outcome variables of research questions 1 and 2 between the (residential) care homes in The Netherlands when compared to Flanders (Belgium) and which factors are causing the country differences?

4. Which factors are stimulating or inhibiting the implementation of the guideline in the (residential) care homes in The Netherlands and Flanders (Belgium)?

5. What is the compliance of and which barriers are perceived by the nurses and nurse aides in (residential) care homes in The Netherlands and Flanders (Belgium) while implementing the guideline?

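### With the stated intraclass correlation of 0.95, 24 homes of 30 residents do not reach the predetermined 80% power under a two-sided test of a relative 25% improvement

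*Protocol article*

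**What the plan says.** Everything relevant stands in the protocol article, Participants and setting, unless noted.

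- Target: "An a priori power of 80% and a level of significance of 0.05 are predetermined".
- Clustering: "Deff = 1 + [(m - 1) *ρ*]; m = the number of residents in each institution", with ρ defined as the intraclass correlation coefficient. The individually randomized sample size is multiplied by this factor.
- Inputs, attributed to earlier studies: "an intraclass correlation coefficient of 0.95 and a standard deviation (sd) for dental plaque and denture plaque of 0.75 and 0.88 respectively is used".
- Effect: "A 25% improvement of oral hygiene level is the presumed effect of the intervention". No baseline or control mean is given.
- Result: "a sample size of 360 residents and 12 clusters per country seems an achievable number for the 6-months period", which is 30 residents per home. The same section says that the cohort of 30 per home rests on the power calculation.
- Score ranges (Oral examination): 0-3 for natural teeth, 0-4 for dentures.

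The oral hygiene level is the primary outcome (Design of the study).

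**The concern.** An ICC of 0.95 in this formula means that 95% of the variance in plaque scores lies between homes. Residents of one home would be nearly interchangeable, and 30 of them would add little to one. The trial would then have roughly as many independent observations as homes, which is hard to square with 80% power for a 25% improvement.

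The planned power for the primary outcome is at stake. If 0.95 is a true between-home correlation, the target is missed by a wide margin at mid-scale baseline means. If it is not, the printed calculation does not describe the trial. In both cases a reader facing a null result cannot tell whether the trial had a fair chance of showing the effect.

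**Working it through.** **Inputs from the article:** ρ = 0.95; m = 30; 24 homes (12 per country); SD 0.75 (natural teeth) and 0.88 (dentures); α = 0.05; power 80%; improvement 25%; score ranges 0-3 and 0-4.

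**Assumptions:** equal allocation of homes; two-sided test; 25% relative to the baseline mean; no baseline adjustment; no dropout; every resident contributes to the index in question. The last two favour the plan.

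**The plan's own figure.** The article prints no unadjusted sample size, design-effect value or absolute difference, so 360 per country cannot be rebuilt step by step. It can be tested against the printed inputs.

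**1. Design effect.** 1 + 29 × 0.95 = 28.55. Effective sample size: 720/28.55 = 25.2 pooled; 360/28.55 = 12.6 per country.

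**2. Detectable difference at 80% power.** δ = √(4 × 7.849 × SD² / n_eff), where 7.849 = (1.960 + 0.842)². Dividing δ by 0.25 gives the baseline mean at which it would be a 25% improvement.

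| Index | Level | δ | Baseline mean needed | Scale maximum |
|---|---|---|---|---|
| Natural teeth | pooled | 0.84 | 3.35 | 3 |
| Natural teeth | per country | 1.18 | 4.73 | 3 |
| Dentures | pooled | 0.98 | 3.93 | 4 |
| Dentures | per country | 1.39 | 5.55 | 4 |

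Three of the four are off the scale. For the fourth, a score on 0 to U with mean μ has variance of at most μ(U − μ). Setting this equal to SD² gives the highest possible mean: 2.80 for natural teeth and 3.80 for dentures. So 3.93 is also out of reach.

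**3. Best attainable power.** At those ceilings the differences are 0.25 × 2.80 = 0.70 and 0.25 × 3.80 = 0.95. The standard error is SD × √(4/n_eff).

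| Index | Level | Standard error | Power, normal | Power, t on homes |
|---|---|---|---|---|
| Natural teeth | pooled | 0.299 | 65% | 61% (22 df) |
| Dentures | pooled | 0.350 | 77% | 74% (22 df) |
| Natural teeth | per country | 0.422 | 38% | 32% (10 df) |
| Dentures | per country | 0.496 | 48% | 41% (10 df) |

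At an assumed baseline mean of 2.0 (difference 0.5), pooled power is 36-39% for natural teeth and 28-30% for dentures.

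**4. More residents per home would not help.** At ρ = 0.95 the effective sample size of 24 homes cannot exceed 24/0.95 = 25.3, however many residents each home supplies.

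**5. Sensitivity to the ICC.** The value 0.20 is assumed for illustration and comes from no document. Design effect = 1 + 29 × 0.20 = 6.8. Ranges run from t-based to normal.

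| Assumed baseline mean | Level | Natural teeth | Dentures |
|---|---|---|---|
| 2.0 | pooled | 91-93% | 80-83% |
| 1.5 | pooled | 69-73% | 55-59% |
| 2.0 | per country | 59-68% | 46-54% |

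**The case against.** **The 80% is a target.** The article calls it predetermined, mentions uncertainty in the calculation and calls the size achievable. This stands as to wording: no achieved power is claimed. But the same section rests the 30 residents per home on the power calculation, so it does present the size as answering the target.

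**The failure depends on unstated readings.** This stands in part. Sidedness is not given, and 25% could mean a quarter of the full scale.
- A quarter of the denture scale (1.0 point) gives 81% pooled by the normal approximation but 78% by t. For natural teeth (0.75) it gives 71% and 67%.
- One-sided at 5%, a 0.75 difference for natural teeth gives 81% (78% by t). Dentures pass 80% once the difference exceeds about 0.87, a baseline near 3.5 of 4.

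These are pooled corner cases without dropout. None reaches 80% per country: the most favourable, one-sided with 1.0 point on dentures, gives 1.0/0.496 − 1.645 = 0.37, about 64%. The first research question, "Is there any statistically significant difference between oral hygiene levels of elderly residents", points to a two-sided test. Adjustment for baseline could raise power, but the printed design effect does not include it. A reader might infer failure under every conceivable reading; the documents support it only under the stated conditions.

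**An article condenses the protocol.** This stands against complaining about missing working steps. It does not answer the point, because the ICC, the formula, the target and the size are all printed.

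**0.95 looks like an examiner-reliability coefficient.** A reader might infer this from its size. The article attributes the value to previous studies, and its own examiner reliability is still to be determined in a pilot study (Data collection). A misprint is equally possible.

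**Conclusion.** The point holds in conditional form. Under the printed ICC, formula, SDs and size, and the assumptions listed in the check, 80% power is not reached at any baseline mean that the score ranges and SDs allow. The ceilings are 61-65% (natural teeth) and 74-77% (dentures) pooled, and 32-38% and 41-48% per country. Dropout would not improve them.

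Two stronger conclusions are tempting and unsupported. One is that the trial is in fact badly underpowered: that needs 0.95 to be a genuine between-home correlation, which the article does not establish. The other is that a lower ICC would make the size adequate. At an assumed ICC of 0.20 the pooled comparison is adequate, or nearly so, at a baseline mean of 2.0, but not at 1.5, and the per-country comparison is inadequate even at 2.0. What is established is that the printed inputs contradict the target, so the trial's actual power is unknown.

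**What to change.** 1. Check the source of 0.95. Replace it with a sourced between-home ICC for plaque; or, if it measures something else, label it as such and take it out of the design effect.
2. State, for each index, the baseline mean that turns 25% into points, and whether the test is two-sided.
3. Restate power or the detectable difference for the fixed 24 homes of 30 residents, pooled and per country, for natural teeth and dentures separately, over a range of ICCs and baseline means, with t-based degrees of freedom. Allow for dropout and for residents who contribute to only one index.
4. If 0.95 is kept, withdraw the 80% figure.
5. Do not state that the size is adequate at lower ICCs unless the restated figures show it for the comparison in question.

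The cost is one rewritten paragraph and possibly a less favourable stated power. The correction itself calls for no extra homes or residents; it does not show that the present number is enough.
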